## Abstract

**Background:**

Work related upper limb disorders constitute 45% of all occupational diseases and are a significant public health problem. A subgroup, non specific arm pain (NSAP), remains elusive in terms of understanding its pathophysiological mechanisms with its diagnosis based on the *absence *of specific clinical findings. One commonly proposed theory is that a neural tissue disorder is the primary dysfunction in NSAP and findings from previous studies lend some support to this theory. However, it is not clear if changes identified are simply a consequence of ongoing pain rather than due to specific neural changes. The presence of neuropathic pain has been investigated in several other musculoskeletal conditions but currently, there is no specific diagnostic tool or gold standard which permits an unequivocal diagnosis of neuropathic pain. The purpose of this study is to further describe the somatosensory profiles in patients with NSAP and to compare these profiles to a group of patients with MRI confirmed cervical radiculopathy who have been previously classified as having neuropathic pain.

**Methods/Design:**

Three groups of participants will be investigated: Groups 1 and 2 will be office workers with either NSAP or cervical radiculopathy and Group 3 will be a control group of non office workers without upper limb pain. Participants will undergo a clinical assessment, pain questionnaires (LANSS, Short Form McGill, DASH and TSK) and quantitative sensory testing comprising thermal detection and pain thresholds, vibration thresholds and pressure pain thresholds.

**Discussion:**

The spectrum of clinically suspected neuropathic pain ranges from more obvious conditions such as trigeminal neuralgia to those with vague signs of nerve disorder such as NSAP. A thorough description of the somatosensory profiles of NSAP patients and a comparison with a more defined group of patients with evidence of neuropathic pain will help in the understanding of underlying neurophysiology in NSAP and may influence future classification and intervention studies relating to this condition.

## Background

Work related upper limb disorders (WRULD) (often called repetitive strain injury) are a significant public health problem, estimated to constitute 45% of all occupational diseases [1]. Non specific arm pain (NSAP) constitutes a subgroup of WRULD [2-5] and has been defined as diffuse pain in the forearm (which can also involve the neck, arm, wrist and hand) in the absence of evidence of a specific upper limb disorder [2-6].

### Aetiology of NSAP

NSAP is a vague clinical entity, the pathophysiological mechanisms of which remain unclear. While it is quite feasible that pain in NSAP is nociceptive in origin e.g. from muscle tissue, an underlying dysfunction of the nervous system has been proposed [7-9]. A mechanisms based approach to understanding pain has been advocated [10] but currently, there are no gold standards or valid or reliable methods to diagnose underlying neurophysiological pain mechanisms. It is proposed that the use of a pain mechanisms classification system would be valuable in identifying sub-groups of patients who are most likely to require different treatment strategies [10]. There is some evidence to suggest that patients treated according to symptom specific classification systems have superior outcomes to those who are not [11].

A number of algorithms for assessing the presence of neuropathic pain exist. They include the use of pain questionnaires and combinations of pain descriptors and clinical testing [12-14]. Treede et al's [14] proposed algorithm for the assessment of neuropathic pain involves the development of a working hypothesis of "possible" neuropathic pain based on clinical information, pain mapping and history relating to the onset of pain. If further evidence by way of clinical examination, neurophysiological tests and laboratory tests such as MRI can be yielded, then patients can be categorised further as "probable" or "definite" neuropathic pain. However, this model requires further testing in terms of reliability and validity. In addition, there are a number of pain questionnaires for the classification of neuropathic pain (e.g. Leeds Assessment for Neuropathic Signs and Symptoms (LANSS), Neuropathic Pain Questionnaire, pain DETECT). Again, all of these methods require further validation before their use as a diagnostic tool can be advocated.

Another means of assessing pain mechanisms is the use of quantitative sensory testing (QST). QST is useful in quantifying mechanical and thermal allodynia and hyperalgesia and may help to characterise painful neuropathic syndromes as well as clarifying some of their pathophysiological mechanisms [15]. However, QST alone cannot conclusively determine the presence of neuropathic pain.

### Evidence for the presence of Neuropathic Pain in NSAP

In relation to the clinical presentation in NSAP, many researchers have reported presenting symptoms which are consistent with those of neuropathic pain, for example, paraesthesia, dysaesthesia, weakness, burning pain, cramping, slowing of fine movements and allodynia [5-9,16,17]. This has led to the initial hypothesis that NSAP may have an underlying neuropathic pain component. Clinical studies have identified the presence of mechanical hyperalgesia involving the peripheral nerve trunks in this population [16-19]. Peripheral nerve trunk mechanical hyperalgesia is tested using upper limb neurodynamic tests and these have been identified as useful indicators of central nervous system hyperexcitability [20]. They may also be reflective of localised peripheral nerve inflammation [21] or indicative of peripheral nerve sensitisation [12]. Smart et al., (2009) [13] have found neural tissue provocation tests for the lower limb (straight leg raise) a useful indicator of peripheral nerve sensitisation while Scholz et al., (2009)[22] have also identified the straight leg raise test within a battery of tests as useful for the differentiation of neuropathic pain mechanisms in LBP. However, the correlation of neurodynamic tests with qualitative measures of pain and quantitative measures of nerve function or indeed the presence of neuropathic pain is unknown in NSAP.

Various QST measures have been used to investigate the somatosensory profiles of patients with NSAP; however the results of these studies reveal conflicting evidence. Greening et al., [23,24] have identified changes in flare response, vasoconstriction and vibration in office workers with NSAP when compared with office workers without pain or non office workers. Their findings in relation to vibration are supported by some researchers [25-28], but not others [29,30].

### QST findings in musculoskeletal disorders

While pressure pain thresholds or thermal QST have not been specifically investigated in NSAP, studies of other working populations have yielded mixed results. Increased sensitivity to pressure has been found in the shoulder and neck muscles of butchers [31], secretaries [32] and manufacturing workers [33]. Contrary to this, Johnston et al., [34] found office workers with neck pain showed no difference in pressure pain thresholds (PPT) over the neck muscles in comparison to controls but they did have lower PPT at median nerve and tibialis anterior sites. Increased sensitivity to pressure has also been found in whiplash and cervical radiculopathy patients [35,36]. In relation to thermal QST, Johnston et al., [34] found that office workers with mild neck pain and disability had decreased heat pain thresholds and were more sensitive to cold pain than controls or office workers without pain. Furthermore, alterations in thermal detection thresholds have been found in the upper limbs of patients with whiplash and cervical radiculopathy [37]. One interesting finding in this study by Chien et al. is the presence of non-symptomatic to symptomatic side differences in the cervical radiculopathy group which did not exist in the whiplash group. Whilst further investigations are warranted to elucidate the significance of this finding, it may reflect a difference between neuropathic versus non-neuropathic pain presentations.

Recent investigations into work related neck pain [34]; diffuse upper limb pain [28], low back pain [38], whiplash [20,36], patellofemoral pain syndrome [39], fibromyalgia and complex regional pain syndrome [40] have shown that these conditions may have a neuropathic pain component. However, many of these studies show positive findings on both the asymptomatic and symptomatic sides, indicating that change may just be reflective of alterations in somatosensory processing associated with pain i.e. central plasticity from nociceptive or inflammatory pain as opposed to true neuropathic pain [14].

Clearly, there is much debate as to whether NSAP, which appears to have features of neuropathic pain, is indeed a neuropathic disorder. Furthermore, there are currently no gold standards with which to classify pain as definitively neuropathic. The purpose of this study is to comprehensively describe the somatosensory profiles in patients with NSAP and to compare them to somatosensory profiles in asymptomatic subjects and subjects with cervical radiculopathy. It is hypothesised that some of the NSAP group may demonstrate a similar presentation to that of cervical radiculopathy, indicating a probable neuropathic pain presentation.

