### Participants

One hundred and fifty consenting male and female subjects, aged 18-65 years will be recruited comprising three equal groups of (1) Patients with NSAP, (2) Patients with cervical radiculopathy and (3) Age and gender matched controls.

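### Resemblance to cervical radiculopathy is read as probable neuropathic pain, but the three-group design cannot separate that from a general effect of pain

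*Protocol article*

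**What the plan says.** All references are to the protocol article.

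- **Hypothesis** (last paragraph of the Background, under QST findings in musculoskeletal disorders): "some of the NSAP group may demonstrate a similar presentation to that of cervical radiculopathy, indicating a probable neuropathic pain presentation". No measure, number of measures or degree of closeness is given.
- **Rival explanation** (same section): where changes appear on both the painful and the painless side, "change may just be reflective of alterations in somatosensory processing associated with pain i.e. central plasticity from nociceptive or inflammatory pain". The Abstract raises the same doubt about earlier NSAP findings.
- **Limits of the measurements** (Aetiology of NSAP): "QST alone cannot conclusively determine the presence of neuropathic pain".
- **Meaning of 'probable'** (Aetiology of NSAP): in the grading algorithm described there, a patient starts at 'possible' and moves to 'probable' or 'definite' on further evidence from clinical examination, neurophysiological tests or laboratory tests such as MRI.
- **Groups** (Participants): 50 NSAP patients (Group 1), 50 with cervical radiculopathy (Group 2) and 50 matched controls (Group 3). Control Subjects requires no significant neck, scapular or shoulder pain in the past year.
- **Analysis** (Statistical Analysis): chi-square tests, and one-way ANOVA with Student-Newman-Keuls comparisons. All of these are tests of difference.
- **Other aids** (Pain Assessment): the LANSS and three pain-mechanism algorithms, including the grading algorithm above, are applied to symptomatic subjects. No section links them to the hypothesis.

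**The concern.** The hypothesis does more than predict a finding. It also says what the finding would mean. The hedge (some of the group, may) covers whether resemblance will be seen. The interpretation that follows carries no hedge beyond the word 'probable', and that word already has a defined use in the same Background.

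The comparison that could test the interpretation is missing. If pain of any origin alters sensory thresholds, NSAP and radiculopathy will both move away from pain-free controls and look alike. If NSAP is neuropathic, the same pattern appears. The pattern cannot tell the two apart.

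The Discussion expects the results to influence later classification and intervention studies. A label of probable neuropathic pain that rests on resemblance could be carried into that work with more weight than the data can bear.

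**Working it through.** The plan gives no figure for this inference, so there is none to reproduce. The check sets the text side by side and then illustrates the logic with numbers.

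**1. What each explanation predicts**

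| Comparison | NSAP is neuropathic | Changes reflect pain in general |
|---|---|---|
| NSAP v controls | differ | differ |
| NSAP v radiculopathy | similar | similar |
| NSAP v a non-neuropathic pain group | may differ | similar |

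Only the third row could separate the explanations, and the study has no such group.

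**2. What the Background says about the measures.** For pressure: "Increased sensitivity to pressure has also been found in whiplash and cervical radiculopathy patients". For thermal testing: "alterations in thermal detection thresholds have been found in the upper limbs of patients with whiplash and cervical radiculopathy". Neither change is described as particular to radiculopathy. The one feature offered as possibly separating neuropathic from non-neuropathic presentations is the "presence of non-symptomatic to symptomatic side differences in the cervical radiculopathy group which did not exist in the whiplash group". That suggestion is itself hedged, and the hypothesis does not use it.

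**3. How far a shared feature can move the probability.** The inputs are assumptions, not figures from the document: 30% of NSAP patients truly neuropathic, and a feature present in 70% of those. Let q be the share of other pain patients who also have it.

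P(neuropathic given feature) = 0.3 × 0.7 / (0.3 × 0.7 + 0.7 × q)

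- q = 0.7: 0.21 / (0.21 + 0.49) = 0.30, so nothing is learned
- q = 0.5: 0.21 / (0.21 + 0.35) = 0.375
- q = 0.1: 0.21 / (0.21 + 0.07) = 0.75

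The result turns on q, and a study without a non-neuropathic pain group cannot estimate q.

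**4. Measures that do not separate radiculopathy from controls.** Suppose NSAP equals controls on a measure, radiculopathy is shifted by D standard deviations, the data are normal with equal SD, and there are 50 per group (Sample size/power calculation). The chance of finding no significant NSAP-radiculopathy difference is:

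| D | Student-Newman-Keuls (simulated, 147 df, 20,000 replicates) | Unadjusted two-sided t-test |
|---|---|---|
| 0 | 97.7% | 95% |
| 0.2 | 89.8% | 83% |
| 0.3 | 77.2% | 68% |

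These rates matter only if non-significance is read as similarity, which the article does not say it will do.

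The hypothesis concerns some individuals, so the individual-level analogue is also useful. The share of NSAP patients, distributed exactly as controls, who fall inside the central 95% range of the radiculopathy group is Φ(D + 1.96) − Φ(D − 1.96). This gives 95%, 92%, 87% and 83% at D = 0, 0.5, 0.8 and 1.0. Resemblance on a weakly separating measure therefore carries little information.

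**The case against.** The strongest reply is that this is a descriptive study. Its objectives are to describe, correlate and compare, and classifying NSAP as neuropathic is not among them. The authors state the limits themselves: no gold standard exists, sensory testing is not conclusive, and changes may only reflect pain. The profile is a composite of neurological examination, pain measures, provocation tests and sensory testing, so it already includes kinds of evidence that the grading algorithm accepts. That algorithm will be applied in any case. Detailed rules on similarity may stand in a full protocol or analysis plan that is not shown.

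Much of this stands, and it rules out several stronger readings that a reader might infer:

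- *That resemblance on any single measure suffices.* The text speaks of a presentation and describes no item-by-item scoring.
- *That sharing a change with whiplash shows it to be non-neuropathic.* The Background lists whiplash among disorders for which studies "have shown that these conditions may have a neuropathic pain component", so whiplash is not a settled non-neuropathic condition here.
- *That radiculopathy fails to differ from controls on some measure.* No section says so. It is a possibility left unguarded, not a documented fact.
- *That the rates above are this study's error rates.* They are illustrations under assumptions.

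What the reply does not answer is the inference itself. The caveats in the Background argue against the interpretation that the hypothesis then adopts. The algorithm grades a patient on that patient's own evidence, and nothing makes that grade, rather than likeness to Group 2, the basis for the word 'probable'. This is a stated conclusion that does not follow, not a detail left to another document.

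**Conclusion.** The point holds in limited form. A presentation similar to radiculopathy does not, in this design, indicate probable neuropathic pain. It is equally compatible with a general effect of ongoing pain, which the document itself proposes, and no comparison group can separate the two. Using 'probable' for group likeness also conflicts with the meaning that the Aetiology section gives the word.

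No numerical size can be attached from the document. The illustrations show only that the strength of the inference depends on how common the same features are in non-neuropathic pain, which the study does not measure. The conclusion rests on the article's own text and not on the assumed values. The descriptive and comparative objectives are unaffected. Only the interpretation needs to change.

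**What to change.** 1. **Background, hypothesis.** State that resemblance to radiculopathy will be reported as consistent with either a neuropathic or a general pain-related change. Use 'probable' only for individuals who reach that grade under the algorithm in Aetiology of NSAP, which Pain Assessment already plans to apply. Keep the article's own caveat that the algorithm needs further testing of reliability and validity.

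2. **Statistical Analysis.** Add that a measure is used as evidence of resemblance only if Group 2 differs from Group 3 on it in this study, and that other measures are reported descriptively. State two limits alongside the rule. First, the filter removes uninformative measures but does not make the remaining ones specific to neuropathic pain. Second, neurodynamic tests will tend to pass it because positive tests are part of how Group 2 is selected (Screening and Allocation to study groups).

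The cost is wording in two places, with no new data or participants. The price is a weaker claim that rests on fewer measures. The first change matters most, because the second does not resolve the ambiguity between the two explanations.

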## Methods/Design

### Objectives

The objectives of this study are to:

• Describe the somatosensory profiles of subjects with NSAP in terms of neurological examination, qualitative measures of pain, neural tissue provocation tests and QST.

• Describe impairment and disability associated with NSAP by means of the Disabilities of the Arm, Shoulder and Hand (DASH) and SF-36 questionnaires.

• Investigate for correlations between clinical examination findings, QST profiles and questionnaire derived pain profiles in subjects with NSAP.

• Compare somatosensory profiles of subjects with NSAP to those with cervical radiculopathy and asymptomatic controls.

### Study design

A case-control observational design will be used to assess quantitative and qualitative sensory features as well as pain profiles in two patient groups and a control group.

### Ethical Approval

The study was approved by the Human Research Ethics Committee - Life Sciences in University College Dublin on January 23rd 2009.

### Participants

One hundred and fifty consenting male and female subjects, aged 18-65 years will be recruited comprising three equal groups of (1) Patients with NSAP, (2) Patients with cervical radiculopathy and (3) Age and gender matched controls.

#### • Groups 1 and 2: NSAP and Cervical Radiculopathy subjects

##### Inclusion criteria

All participants from patient groups will be office workers who have significant unilateral upper limb pain as defined by a numerical rating score of ≥ 3/10 [31,41], who spend more than 40% of their working week using desktop equipment [24] and have been in their current employment or similar (i.e. involving office work/keyboard operation) for at least two years [34]. More specific information regarding diagnostic criteria for each patient group is outlined in the next section. Patients will be recruited from local orthopaedic outpatient and occupational health departments of Dublin hospitals and physiotherapy practices and also from the staff and student population of University College Dublin.

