#### • Group 3: Control Subjects

##### Inclusion criteria

Fifty age and gender matched subjects will be included if they have no history of significant neck, scapular or shoulder pain over the past 12 months (significant pain is defined as pain ≥ 3/10 on a visual analogue scale [31,41] and do not use desktop equipment for more than 40% of their working week [24]. The control group will be recruited from staff/students at University College Dublin, St Vincent's University Hospital staff and the local community.

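### Controls are screened on present desktop use and a 12-month neck, scapular and shoulder history, so someone who left desk work because of arm pain can enter the reference group.

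*Protocol article*

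**What the plan says.** **Patients.** The inclusion criteria for Groups 1 and 2 state that "All participants from patient groups will be office workers who have significant unilateral upper limb pain". They must be people "who spend more than 40% of their working week using desktop equipment [24] and have been in their current employment or similar", where similar employment is explained as "i.e. involving office work/keyboard operation) for at least two years [34". The 40% share is in the present tense; the two-year condition is about job tenure.

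**Controls.** The inclusion criteria for Group 3 require that they "do not use desktop equipment for more than 40% of their working week [24" and have "no history of significant neck, scapular or shoulder pain over the past 12 months", with significant pain set at 3/10 or more. No period of past desk work is asked about.

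**Descriptions elsewhere.** The abstract says that "Group 3 will be a control group of non office workers without upper limb pain". The Objectives include "Compare somatosensory profiles of subjects with NSAP to those with cervical radiculopathy and asymptomatic controls" and also "Describe impairment and disability associated with NSAP by means of the Disabilities of the Arm, Shoulder and Hand (DASH) and SF-36 questionnaires".

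**General exclusions.** Among other conditions, these remove people seeking compensation, people with bilateral upper limb pain, and people with earlier surgery or trauma to the upper quadrant. Past or present unilateral arm pain and a pain-driven change of work are not listed.

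**The concern.** Arm pain is a plausible reason to give up or cut back keyboard work. A classification by present desktop use can therefore be altered by the condition under study. If a person whose arm pain led them away from a desk is later counted as an unexposed, healthy control, the reference group contains former cases. Should their sensory thresholds still resemble those of patients, the difference between NSAP and controls shrinks. That comparison is a stated objective.

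A second, smaller matter lies on the patient side. The disability objective (DASH, SF-36) is about NSAP generally, but a patient whose pain has brought desk use down to 40% or less does not qualify.

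**Working it through.** **Step 1. Set the control rules against three hypothetical people.**

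| Person | Desktop use 40% or less now | No neck, scapular or shoulder pain of 3/10 or more in 12 months | General exclusions | Admitted by the written criteria? |
|---|---|---|---|---|
| Left desk work because of arm pain, symptom-free for 13 months | met | met | none applies | yes |
| Cut desk work because of unilateral forearm pain, still present, neck and shoulder clear | met | met | none applies (pain is not bilateral) | yes on the literal wording, against the abstract and Objectives |
| Cut desk work because of shoulder pain of 3/10 or more within 12 months | met | not met | not needed | no |

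The second row arises because the control look-back names neck, scapula and shoulder, while Table 1 (classification criteria for NSAP) places the pain in the forearm. The look-back thus leaves out the site that defines the main patient group.

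**Step 2. Does any other rule close the gap?** The two-year tenure rule applies to patients only. The Data Collection section records work status and current hours on desktop, laptop and mouse equipment; it mentions neither earlier exposure nor the reason for any reduction. Nothing shown closes the first row.

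**Step 3. Size, as an illustration only.** The one figure that the plan supplies is its target: effect size 0.5, power 0.8, two-tailed 0.05, 50 per group. Checking that baseline for two groups gives n = 2(1.960 + 0.842)²/0.5² = 62.8, so 63 per group. With 50 per group, two-sided t-test power is about 0.70. The stated sample size is a separate matter; the 0.70 serves here only as a starting point.

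Assume that a share m of controls carry the patient mean. The expected difference is then 0.5 × (1 − m), ignoring the small added variance from mixing.

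| Assumed m | Effect | t-test power, 50 per group, two-sided |
|---|---|---|
| 0% | 0.50 | 0.70 |
| 5% | 0.475 | 0.65 |
| 10% | 0.45 | 0.61 |
| 20% | 0.40 | 0.51 |

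No value of m can be derived from the documents. Nor do they say that people free of symptoms for a year keep abnormal thresholds. If they do not, former cases cause no dilution.

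**The case against.** **The barred patients and the admitted controls are mostly different people.** A reader might infer that the 40% rule turns away symptomatic patients and lets those same people in as controls. The documents do not support this in general. Recent neck, scapular or shoulder pain bars a control, and the abstract and Objectives call for pain-free controls. The person symptom-free for 13 months could not be a patient under any exposure rule, for lack of current pain. This objection stands. What remains is the former case and, on the literal control wording only, the person with forearm pain.

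**Screening would catch current pain.** Under Group Selection, all participants other than those with radiculopathy have pain mapping and a clinical examination, and how the questions are put may be set out in the full protocol. Current forearm pain would probably be found. But the written control criteria do not make it a reason for exclusion, and resolved pain that led to a change of work would not show on a pain map.

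**Present use only is too broad a description for patients.** They also need two years' tenure, and a share of the working week may be read as the usual week, so someone on short sick leave is not clearly excluded. This stands. It does not help a long-serving worker on lastingly reduced duties.

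**Studying active office workers is a sourced design choice.** This also stands. The consequence is narrower generalisability, which is neither a contradiction nor an error. Using recalled pre-onset exposure would admit people long out of desk work and add heterogeneity.

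**Conclusion.** The point holds for the control group. As written, the criteria do not keep out people who left or reduced desk work because of upper limb pain, and their list of pain sites does not match the pain-free controls described in the abstract and Objectives. The likely effect is dilution of case-control differences. Its size is unknown, and the table above rests wholly on an assumed share and on assumed persistence of abnormal thresholds. This is a cheap improvement to eligibility wording and does not undermine the design.

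On the patient side, the NSAP disability description applies to people still doing substantial desk work. That is a limit to be stated.

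Two stronger readings are not supported:

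- A reader might infer that the 40% rule trims severe radiculopathy more than severe NSAP, because the former come from a spinal surgery service, and so favours the hypothesis. Nothing shows unequal loss, the same rule applies to both groups, and the hypothesis is that some NSAP patients resemble radiculopathy, which is not a claim about group means.
- A reader might compute that losing the most severe 10% to 30% lowers mean severity by 0.19 to 0.50 SD and, at correlations of 0.3 to 0.5, moves sensory means by 0.06 to 0.25 SD. The arithmetic is right, but every input is assumed, including that work status sorts patients perfectly by severity. Between the two patient groups only the difference in shifts matters, and it is zero if losses are equal.

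**What to change.** 1. In the control inclusion criteria, exclude anyone who left or reduced desk work because of upper limb pain. One screening question suffices.
2. Reconcile the control pain criterion with the abstract and Objectives, so that the sites it names agree with a group described as free of upper limb pain and asymptomatic.
3. Under Study Limitations, state that the patient groups, and hence the description of NSAP disability, represent people still spending more than 40% of the working week at desktop equipment.
4. Optionally, apply the 40% criterion to the period before symptom onset or before a pain-related change of duties. This is a trade-off, for the reasons given above.

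The cost of items 1 to 3 is wording, one question, reliance on the person's recall of why their work changed, and the loss of a few candidate controls. No visit or test is added.
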